# Monitoring of Pregnant Women Using the “Risk Identification, Evaluation Counseling, Systematic Monitoring, Troubleshooting” (REST) Mobile App: Protocol for a Cluster Randomized Controlled Trial

**DOI:** 10.2196/66774

**Published:** 2025-08-06

**Keywords:** pregnant woman, midwife, antenatal screening, mobile health, mHealth, application, app, randomized controlled trial, RCT, antenatal class, risk identification, evaluation counseling, systematic monitoring

## Abstract

**Background:**

The maternal mortality rate (MMR) in Indonesia is still quite high and has not reached the national target. The success of maternal health programs can be assessed through the main indicator of the MMR. Pregnancy monitoring is one of the efforts to reduce the increase in the MMR.

**Objective:**

This study aims to improve maternal and child safety and health during pregnancy and childbirth through pregnancy monitoring using a mobile app called REST (Risk Identification, Evaluation Counseling, Systematic Monitoring, Troubleshooting).

**Methods:**

The research used the cluster randomized controlled trial (RCT) design, involving pregnant women from 11 subdistricts in Purworejo Regency, who were randomized to 11 clusters in the intervention group and 11 clusters in the control group. The 22 ANC class clusters comprised 22 midwives and 220 pregnant women. The intervention group received monitoring using the REST mobile app, while the control group received standard pregnancy monitoring in the antenatal care (ANC) class. The mentoring program included the use of the REST mobile app, which consists of pregnancy checks according to the 10T pregnancy examination standard. The app was used by midwives and pregnant women, starting from the second trimester of pregnancy to childbirth.

**Results:**

In July 2023, the REST mobile app was prepared and tested in small community groups, including midwives and pregnant women, through simulation, and in September 2023, the app was further refined based on feedback from these groups and introduced to study participants. The majority of participants were aged 20-35 years (n=168, 76.4%), consistent with national demographic trends. Approximately 185 (84.1%) had secondary education (junior and senior high school), and 57 (25.9%) had tertiary education (college graduates). The participants were evenly distributed across economic quintiles, reflecting diverse socioeconomic backgrounds, and most lived approximately 1 km from a health facility. Ethical approval was obtained in April 2024. Staff training was conducted from July to October 2023. Participants were recruited from November 2023 to January 2024, the intervention was implemented from February to July 2024, and data were collected from August 2024 to February 2025. Data were analyzed in April 2025, and dissemination of results is expected by the end of 2025.

**Conclusions:**

Pregnancy monitoring using the REST mobile app is expected to have a significant influence on the number of ANC visits, reduce pregnancy complications, improve normal delivery methods, and ensure the birth weight of the baby stays within normal limits (≥2500 g).

**Trial Registration:**

ClinicalTrials.gov NCT05741931; https://clinicaltrials.gov/study/NCT05741931

**International Registered Report Identifier (IRRID):**

DERR1-10.2196/66774

## Introduction

The success of maternal health programs can be assessed through the main indicator of the maternal mortality rate (MMR). The gestation period is the focus of the main problem in preventing high MMRs, as it is during this time that the majority of risk factors for adverse maternal and fetal outcomes emerge. In particular, nutritional and metabolic issues, such as hypocalcemia, have been associated with complications in pregnancy, especially in resource-limited settings [1-3]. The gestation period is the focus of the main problem in preventing high MMRs. The World Health Organization (WHO) recommends that health workers improve consultation and care for pregnant women [4].

Antenatal care (ANC) services in normal pregnancy are provided at least 6 times: 2 times in the first trimester, 1 time in the second trimester, and 3 times in the third trimester. ANC examinations in normal pregnant women are carried out by a doctor at least 2 times in the first and third trimesters [5]. Failure in pregnancy care or ANC usually occurs due to social and economic factors, such as low education and family income, being too young or too old, living far from health facilities, unwanted pregnancy, and the consumption of illegal drugs [4].

The MMR in Central Java Province in 2021 was 199 per 100,000 live births (1011 cases), an increase compared to the MMR in 2020 of 98.6 per 100,000 live births (530 cases) and in 2019 of 76.93 per 100,000 live births (416 cases). Cases of maternal mortality increased from 2019 onward. The cause of disruption in maternal and child health services during the pandemic was due to major changes in health facility services and public health [6]. The still high mortality rate shows that the quality of maternal and neonatal services is not optimal. The issue of “3 late” is still the main problem in maternal health services, namely late decision-making, late arrival at the referral point, and late getting the services needed at health facilities. The low quality of pregnancy examination services is also reflected in the low compliance with ANC standards, which include 10 pregnancy examinations [7].

There are several studies on pregnancy using mobile apps, such as the m4Change app [8], which contains health promotion around maternal and child health, with the results of improving the quality of ANC. The PANDA (Pregnancy and Newborn Diagnosis Assessment) app is used to monitor during ANC, with the results of knowing the cause of pregnancy complications [9]. The Innovative Mobile Phone Technology for Community Health Operations (ImTeCHO) app for scheduling home visits, screening for complications, and counseling has effective results in areas that are difficult for health facilities to reach [10]. This mobile app can be used as a medium by pregnant women to monitor their pregnancy and by midwives who conduct pregnancy checks. Mobile apps should be used by considering their effectiveness and quality of use.

Pregnancy monitoring is a decision-making action for pregnant women and their fetuses in order to overcome previous adverse events in fetal development. Pregnancy monitoring facilitates early discovery of abnormal developments and complications and supports timely intervention so that early treatment can be administered and disorders and risks for pregnant women reduced. If pregnancy disorders are found in the mother and fetus, efforts are made to reduce the high risk in pregnancy [11].

Pregnancy monitoring is one of the efforts made by both health workers and health cadres in monitoring the condition of both mother and fetus during pregnancy, as it plays a critical role in early detection of complications and improving maternal outcomes. Monitoring by health care providers during the gestation period, such as to provide accurate real-time data on how many pregnant women are enrolled in ANC and what the ANC class characteristics, interventions, and outcome approaches are, will improve ANC information systems that can reduce maternal mortality cases [12].

An assessment of the implementation of health services for pregnant women can be carried out by looking at the K1, K4, and K6 coverage. K1 coverage is the number of pregnant women who have received ANC services for the first time by health workers compared to the target number of pregnant women in 1 work area within a period of 1 year. K4 coverage is the number of pregnant women who have received ANC services in accordance with the standard at least 4 examinations according to the recommended schedule in each trimester compared to the target number of pregnant women in 1 work area within 1 year. K6 coverage is the number of pregnant women who have received ANC services in accordance with the standard of at least 6 examinations and at least 2 doctor’s examinations according to the recommended schedule in each semester compared to the target number of pregnant women in 1 work area within a period of 1 year. This indicator shows access to health services for pregnant women and the level of compliance of pregnant women in checking their pregnancy with health workers [5]

The ANC class is an effort by the Government of Indonesia to promote health and prevent maternal and infant mortality. The Government of Indonesia began implementing the ANC class program in 2009. The program aims to increase the understanding of pregnancy, the use of ANC and postpartum family planning services, and awareness of infectious diseases. The target population of the ANC class is mothers with a gestational age of 22-36 weeks. Each class consists of a maximum of 10 pregnant women and is facilitated by midwives or health workers who have received training in ANC [13]. Mobile apps have been widely used by various groups, such as health cadres, health service users, and health service providers, to facilitate activities in the health sector [14].

Mobile apps for health are often used to improve the quality of health services. Mobile apps can continue to evolve through the correction of errors adjusted to needs [15]. There are many variations of mobile apps used for health purposes. They can contain patient medical records, health consultations, and health training, as well as health promotion [16,17]. Pregnant women make up a significant proportion of the world’s population. With an average age of 30 years, pregnant women are a generation that wants to get to know new technologies and expand medical care in the digital sector. There are many types of mobile apps used in monitoring the health of pregnant women. These apps are often used in the field of midwifery because they are considered appropriate and easy to implement. They are used not only for pregnant women but also for several groups involved, including couples and families. Pregnancy-related mobile apps for postnatal care and parenting have also been developed. The success in modifying a pregnancy-related app and complying with its use make it a new lifestyle intervention for users [18].

Based on the aforementioned findings, it is important to conduct research on the use of mobile apps for pregnancy monitoring. The objectives of the study are to check for the presence of pregnancy complications, compare the intervention and control groups in the context of the number of pregnant women who give birth normally, ensure that the birth weight of babies reaches ≥2500 g, and improve the number of ANC visits to ≥6.

The benefits achieved from the results of the study are making it easier (1) for pregnant women monitor their pregnancy conditions and (2) for village midwives to be able to assist in monitoring maternal health during pregnancy, recognizing maternal problems, and helping make timely referrals. The benefits for related agencies are input for public health centers, the independent practice of midwives and doctors, the Health Office, and the regional general hospital in monitoring pregnant women to prevent maternal and infant mortality. The benefits for researchers include motivating and facilitating community leaders, cadres, and communities, as well as increasing cross-sector cooperation in monitoring the health of pregnant women. For science, conducting pregnancy monitoring can be a novelty.

## Methods

### Study Design

This research is an experimental study with a cluster randomized controlled trial (RCT) design. Cluster RCT is a research design that has multilevel characteristics. Generally, cluster RCT research uses 2 levels, the cluster or group level and the individual level. In this study, the class cluster will include pregnant women and participants of the ANC class. To minimize the risk of selection bias, we implemented the following strategies: (1) randomization at the cluster level was performed after cluster enrollment, and baseline characteristics of participants across the intervention and control groups will be carefully assessed and reported. The research design is described in Table 1.

**Table 1 table1:** Research design.

Group	Activity sequence 1			Activity sequence 2			Activity sequence 3			Activity sequence 4
	Observation	Intervention	Observation		Intervention	Observation		Intervention	Observation	
Control	O_0_^a^	X_0_^b^	O_1_^c^		X_0_	O_2_^d^		X_0_	O_3_^e^	
Intervention	O_0_	X_1_^f^	O_1_		X_2_^g^	O_2_		X_3_^h^	O_3_	

^a^O_0_: early identification in pregnant women in the first class of pregnant women.

^b^X_0_: standard intervention for routine antenatal classes without an app.

^c^O_1_: observations in the second class of pregnant women (trimester 2).

^d^O_2_: observations in the third class of pregnant women (trimester 3).

^e^O_3_: observation of childbirth and the newborn.

^f^X_1_: introduction of the REST (Risk Identification, Evaluation Counseling, Systematic Monitoring, Troubleshooting) mobile app for pregnancy monitoring for mothers and midwives using the 10Tpregnancy examination standard.

^g^X_2_: monitoring pregnant women after using the mobile app.

^h^X_3_: monitoring pregnant women using the mobile app and preparing for childbirth during the third trimester.

Assessment of the results of the research will begin from the implementation of the first class of pregnant women. The total number of meetings was 3. The final result (a comparison of the expected outcome) was at the time of delivery. The research was carried out after ethical approval was obtained. The research locations are in 11 subdistricts in Purworejo Regency (Central Java, Indonesia): Loano, Purwodadi, Bruno, Butuh, Purworejo, Bagelen, Kaligesing, Kemiri, Kutoarjo, Ngombol, and Pituruh. These 11 subdistricts were chosen because they have health centers with inpatient services that make it easier for pregnant women to give birth in their areas.

Each ANC class group consisted of 10 pregnant women and 1 midwife. In each of the 3 meetings, an examination based on the 10T pregnancy examination standard was conducted, which included measuring the weight and height (T1), blood pressure (T2), mid-upper arm circumference (T3), uterine fundal height (T4), tetanus immunization (T5), iron supplement tablets (T6), fetal presentation and fetal heart rate (T7), counseling (including childbirth and postpartum preparation; T8), hemoglobin levels (T9), and care as needed (T10), as per the policy of the Indonesian Ministry of Health [5]. The results of the examination at each meeting were entered into the REST (Risk Identification, Evaluation Counseling, Systematic Monitoring, Troubleshooting) mobile app, and the pregnant women could see these results. If they performed a self-examination outside the ANC class schedule, they could fill in the results of the examination according to what they knew. Midwives and pregnant women were provided with training and a guidebook module for using the app. The control group carried out the standard ANC class without the use of the app, and they were exempt from recording examination results.

### Population

The target population in this study was all pregnant women in Purworejo Regency. The affordable population was all pregnant women in 11 subdistricts. In total, 14 inpatient health centers were included, which included 22 clusters of ANC classes. Each cluster or class group comprised 10 pregnant women who met the inclusion criteria.

The inclusion criteria were as follows: pregnant women with a gestational age of 20-22 weeks (trimester 2), pregnant women who had a pregnancy examination at a health facility, mothers who planned to stay in the research area for at least the next 2 years, and mothers who were willing to participate in the research by signing an informed consent form.

The exclusion criteria were as follows: chronic diseases that require special pregnancy care, inability to give birth normally, and inability to operate an Android cellphone. The applicant was dropped if she moved outside the research area, could not be contacted after agreeing to provide informed consent, or decided to stop participating in the research.

### Sample Size

The sample size for this study was determined based on the following formula of Lemeshow [19]:

where n is the number of samples per group, Z_1–α/2_=1.96 (at the level of 95% trust), Z_1–β_=0.842 (at 80% power), p_1_ is the proportion of outcomes in the intervention group, p_2_ is the proportion of outcomes in the control group, and p_1_ – p_2_ is the difference between the 2 proportions to be compared.

Based on the calculation of the sample size from previous studies [4,20-22], p_1_=0.92 and p_1_=0.72, so the minimum sample size for the intervention and control groups was 54 respondents each. In cluster RCT research, it is necessary to consider the *design effect* (DE) in determining the sample size. The formula used is DE = 1 + (m – 1), where m=10 (the average number of samples per cluster) and is the intraclass correlation coefficient, assumed to be 0.05.

Based on the calculation results, a DE of 1.45 was obtained. Furthermore, the sample size that was obtained was multiplied by the DE, resulting in a sample size of 78.3, which was rounded to 79 respondents per group. Therefore, the total number of participants needed was 158, although considering a loss to follow-up of ~35% (based on a preliminary study of the attendance of ANC classes in 2019 in Purworejo Regency)*.* Therefore, it was necessary to take a total of 214 (107 participants in the intervention and the control group each) at the beginning of the study through cluster sampling. The number of clusters to be used was 22 groups of pregnant women, so each group needed 9.72 samples, rounded 10 pregnant women in each group.

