### Data Analysis

Descriptive statistics were used to find out the basic characteristics of the entire study group. For bivariable analysis, the independent *t* test or Mann-Whitney U test, and the chi-square test or the Fisher precise test were applied for categorical results, adjusting for group design, if necessary.

Multivariable analysis was performed using mixed effects models to account for clustering at the level of the ANC class cluster. A mixed effects linear regression model was used for sustained outcomes, such as the number of ANC visits and birth weight. Mixed effects logistic regression models were used for binary outcomes, such as pregnancy complications and delivery methods. All models included random interception to account for variations between clusters and fixed effects for interventions, as well as potential confounding variables, including maternal age, education level, socioeconomic status, obstetric history, and nutritional status. Statistical significance was determined using a 2-headed *P* value of <.05.

For each primary and secondary outcome, we used an estimate of the effect size and its precision (95% CIs). Other analyses, including subgroup analysis and customized analysis, of study results were also carried out. Stata 14.0 was used to analyze the data.

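### The 35% loss allowance multiplies by 1.35 instead of dividing by 0.65, so neither 214 nor the 220 enrolled leaves the 158 evaluable women the protocol requires

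*Protocol article*

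**What the plan says.** The Sample Size section sets out every input. The significance level enters as "Z_1–α/2_=1.96 (at the level of 95% trust") and power as "Z_1–β_=0.842 (at 80% power"). The base calculation is given as "p_1_=0.92 and p_1_=0.72, so the minimum sample size for the intervention and control groups was 54 respondents each"; the second proportion is evidently the control value, p2. The design effect uses a class size and correlation described as "where m=10 (the average number of samples per cluster) and is the intraclass correlation coefficient, assumed to be 0.05", which gives 1.45 and raises 54 to 78.3, rounded to 79 per arm.

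The loss allowance follows: "the total number of participants needed was 158, although considering a loss to follow-up of ~35"%, a rate taken from a preliminary study of 2019 class attendance. The section then concludes that "it was necessary to take a total of 214 (107 participants in the intervention and the control group each"). It spreads 214 over 22 classes (9.72 each) and rounds up to 10. The Results section reports 220 women in 22 classes, 11 per arm. The inflation formula is not printed, and no other reason for 214 is given.

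**The concern.** A loss allowance has one purpose: the number enrolled, less the expected loss, should equal the number required. Adding 35% of the required number does not do this, because the 35% is lost from the larger enrolled number. At a rate this high the two calculations differ by 30 women (244 against 214).

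At stake is whether the enrolment figure protects the planned sample under the protocol's own assumption. A reader will take 214, or the 220 enrolled, as enough to withstand 35% loss and still leave 158. If it is not enough, the sample size justification contradicts itself.

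**Working it through.** **Inputs** (Sample Size, unless noted): z = 1.96 and 0.842; proportions 0.92 and 0.72; class size m = 10; intraclass correlation 0.05; loss about 35%; 220 enrolled in 22 classes (Results). The two-sided test agrees with Data Analysis: "Statistical significance was determined using a 2-headed *P* value of <.05".

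**1. Reproducing the plan's figures**
- Variance term: 0.92 × 0.08 + 0.72 × 0.28 = 0.2752.
- Base n per arm, unpooled formula: (1.96 + 0.842)² × 0.2752 / 0.20² = 54.02, stated as 54. The pooled formula gives 57, so the plan used the unpooled one.
- Design effect: 1 + (10 − 1) × 0.05 = 1.45.
- 54 × 1.45 = 78.3, rounded to 79 per arm, 158 in total.
- Loss by multiplication: 79 × 1.35 = 106.65, rounded to 107 per arm, 214 in total. This matches the protocol exactly.
- Loss by division: 79 / 0.65 = 121.5, rounded to 122 per arm, 244 in total. This does not match.

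**2. What remains after 35% loss**

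| Enrolled | Evaluable at 35% loss | Against 158 | Loss at which 158 remain |
|---|---|---|---|
| 214 | 214 × 0.65 = 139.1 | about 19 short | 1 − 158/214 = 26.2% |
| 220 | 220 × 0.65 = 143 | 15 short (9.5%) | 1 − 158/220 = 28.2% |
| 244 | 244 × 0.65 = 158.6 | met | 1 − 158/244 = 35.2% |

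Rounding up to 10 per class therefore helps a little but does not close the gap.

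**3. Power at 35% loss from 220 (71.5 per arm), by the protocol's normal, unpooled method**

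Power = Φ(0.20 / √(0.2752 / n_eff) − 1.96), where n_eff = n / design effect.
- Design effect kept at 1.45: n_eff = 71.5 / 1.45 = 49.3; the ratio is 2.677; power is about 76%.
- Loss even across classes, so 6.5 women per class: design effect = 1 + 5.5 × 0.05 = 1.275; n_eff = 71.5 / 1.275 = 56.1; the ratio is 2.855; power is about 81%. On this basis 54 × 1.275 = 68.85, so 69 per arm would suffice.

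**4. Sensitivity**
- Uneven loss. The documents give no figure for how class sizes would vary, so a coefficient of variation (CV) is assumed. With design effect = 1 + ((1 + CV²) × 6.5 − 1) × 0.05, a CV of 0.4 gives 1.33 and about 80% power; 0.5 gives 1.36 and about 79%; 0.7 gives 1.43 and about 77%.
- A t reference on 20 degrees of freedom (22 classes minus 2) gives about 72% with design effect 1.45 and about 77.5% with 1.275. This is a different basis from the protocol's. It lowers power even with no shortfall: 79 per arm at 1.45 gives about 76%.

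**The case against.** The strongest reply is that the shortfall in numbers need not be a shortfall in power. The 158 assumes 10 evaluable women per class. Losing 35% of each class also shrinks the classes, and smaller classes carry a smaller design effect. On the protocol's own method, 71.5 per arm in classes of 6.5 gives about 81%. This reply stands, with two limits: the protocol does not make the argument, since it states 158 on a class size of 10, and the 81% needs loss to be even across classes.

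It can also be said that 35% describes class attendance. All outcomes are measured after labour (Study Outcomes), so a woman who misses classes may still contribute data and the true loss may be smaller. That is fair, and it makes 143 a planning figure rather than a prediction. The protocol nevertheless uses 35% as its loss to follow-up, and the arithmetic must follow from that.

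Two stronger readings are tempting, and the documents support neither as part of this error.
- A reader might infer that the analysis covers attenders only, because the Population section says "The applicant was dropped if she moved outside the research area, could not be contacted after agreeing to provide informed consent", or if she chose to leave the research. That rule does not remove women who merely miss classes or stop using the app. Data Management provides for contacting participants or midwives about missing data, and for multiple imputation or complete-case analysis. No section describes access to facility records that could replace missing outcomes.
- A reader might infer that power is clearly below 80% because only 22 classes are randomised. The choice of reference distribution is commonly left to the analysis plan and has nothing to do with the loss allowance.

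**Conclusion.** The point holds as an arithmetic error in a stated figure. Under the protocol's own 35% loss, the enrolment target should be 244, not 214, and the 220 women enrolled leave 143, which is 15 below the stated 158. These results rest only on numbers printed in the protocol.

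The effect on power is small and depends on assumptions. It ranges from about 76% (design effect 1.45 retained) to about 81% (even loss, design effect 1.275) by the protocol's method. It is somewhat below the even-loss figure if loss is uneven, and lower on either basis with a 20-degree-of-freedom reference. The documents give neither the actual loss nor its spread across classes, so they do not show that power falls well below 80%.

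**What to change.** In Sample Size:
1. Replace the inflation step with 79 / 0.65 = 122 per arm, 244 in total.
2. State that the 220 enrolled meet the required 158 only if loss is at most about 28%. This is a limit on numbers against the stated 158, and it should not be presented as the loss at which power drops below 80%.
3. Give power at 35% loss on one consistent basis with its assumptions named. For the normal, unpooled method that is about 76% with the design effect of 1.45 kept, and about 81% with even loss and 1.275. Note that uneven loss or a 20-degree-of-freedom t reference gives somewhat less. The 28% limit should not be paired with power figures from a different reference distribution.

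The cost is a few corrected sentences and a slightly less favourable statement. Recruitment is complete and no extra enrolment is needed.
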